#### Main outcome

Pain and disability will be the main outcomes of the study. Pain will be evaluated through the numerical pain scale, where the participant will be asked about their perception of pain suffered in the last week and will assign a value to it, ranging from 0 to 10, where 0 indicates no pain and 10 indicates worst pain ever felt [11, 23]. Pain will also be assessed by pressure threshold using a pressure algometer device (Fnd-50, PIAB 50-n, Italy) in the lumbar region. The assessment will be conducted specifically on the paraspinal muscles bilaterally at the L1 to L5 levels. Three measurements will be performed at the same point, and the average of the values will be calculated [24]. The distal end of the device will be positioned perpendicularly on the evaluated surface, and constant pressure of 2.55 kg will be applied. Participants will be instructed to indicate the moment when the sensation of pressure changes to a sensation of pain and the value will be recorded. The pain threshold will be defined in kilogram-force (kgf/cm^2^), through the minimum pressure necessary to induce pain in the evaluated region. Still as the main outcome, disability will be evaluated through the Oswestry Disability Questionnaire translated and validated for the Brazilian population [25] composed of ten questions that assess pain intensity and the effect of pain on activities of daily living and classify the individual as minimal (0–20%), moderate (21–40%), severe (41–60%), disability (61–80%), or bed-bound (81–100%) [26].

#### Secondary outcomes

As secondary outcomes, the patient’s global impression of improvement, central sensitization, and biopsychosocial factors will be evaluated. The patient’s overall impression of improvement will be assessed using the 11-point Improvement Percentage Scale, ranging from − 5, indicating “much worse,” to 0 indicating “no change” to +5 “completely recovered” [23, 27], i.e., higher scores correspond to greater recovery. Central sensitization will be evaluated using the Central Sensitization Questionnaire translated and validated for the Brazilian population [28] composed of two parts (A and B), where part A contains 25 statements, scored on a Likert scale from 0 to 4 points, whose final score can vary from 0 t o100 points, with values closer to 100 indicating a greater degree of central awareness. Part B contains a list of 10 medical diagnoses related to central sensitization syndrome, and the subject is asked about the presence/absence and year of diagnosis. Biopsychosocial factors will be evaluated using the STarT Back Toll questionnaire [29] which classifies the risk of poor prognosis of individuals with LBP in the presence of physical and psychosocial factors and is composed of nine items related to referred pain, dysfunction, comorbidities, and psychosocial factors such as catastrophizing, fear, anxiety, and depression that classify the individual as low, medium, and high risk.

In addition, the autonomic nervous system will be evaluated through the heart rate variability (HRV), which will be analyzed using linear methods, in the domains of time (SDNN and RMSSD) and frequency ((LF ms2, LF un, HF ms 2 , HF un and LF/HF) and by the geometric indices (SD1, SD2 and SD1/SD2) [30]. The participant will be invited to lie in the supine position on a stretcher, and the evaluator will place a heart rate monitor (Polar RS800CX) on the individual’s chest, with the objective of recording the heart rate beat by beat for 15 min, for later analysis of the HRV. After capturing the heart rate beat by beat, by the Polar RS800CX heart rate monitor (Polar Electro, Kempele, Finland), the data will be submitted to digital (Polar Pro Trainer software version 5.0) and manual filtering (Microsoft Office Excel version 15.3) to eliminate premature ectopic beats and artifacts [31], and only sets with more than 95% of sinus beats will be included in the study. From the period of greater stability of the tachogram, 1000 consecutive RR intervals will be extracted from the baseline and final moments, followed by the calculation of HRV indices using the Kubius HRV software [32]. For the spectral analysis (LF ms2, LF u.n, HF ms 2, HF u.n and LF/HF), the fast Fourier transform algorithm will be used [33].

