### Outcomes

Participants will be evaluated by a researcher blind to allocation and the evaluative moments for all outcomes will correspond to the pre-intervention (M0), immediately after the last meeting (M1) and reassessed again in the follow-up of four (M2) weeks after the end of the protocols (Fig. 2).

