### Statistical analysis

To analyze the population profile data, we will use the descriptive statistical method and the results will be presented with mean values, medians, standard deviations, minimum and maximum values, and confidence intervals.

Data normality will be determined using the Shapiro-Wilk test, and the comparison of variables between groups at baseline will be performed using Student’s *t*-test for unpaired data for data with normal distribution or the Mann-Whitney test for non-normal data.

Comparisons of primary and secondary outcomes between groups and moments will be performed using the analysis of variance technique for repeated measures model in the two-factor scheme. Repeat measurement data will be checked for sphericity violation using Mauchly’s test, and the Greenhouse-Geisser correction will be used when sphericity is violated.

To analyze the moments, Bonferroni’s post-test for normal distribution or Dunnet’s post-test for non-normal distribution will be used, and the analysis of the different moments between the groups will be carried out using Student’s *t*-test for unpaired data with normal distribution or Mann-Whitney test for non-normal data.

The adopted statistical significance will be set at 5%. Analyses will be performed using the Statistical Package for the Social Sciences software—version 22.0 (SPSS Inc., Chicago, IL, USA) by a researcher blinded to treatments and group allocations using a coded spreadsheet. All the randomized participants will be included in the analysis, in accordance with intention-to-treat principles. To consider all participants, the missing data will be addressed according to the last observation carried forward (M0 or M1) [36]. Analysis and results from this study will be conducted by an independent biostatistician and checked for accuracy.

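### The HRV rule of 1000 consecutive RR intervals cannot be met from a 15-minute recording when the mean heart rate is below about 67 beats/min

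*Protocol article*

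**What the plan says.** All the processing rules stand in the Secondary outcomes section of the protocol article.

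- **Posture:** "The participant will be invited to lie in the supine position on a stretcher".
- **Recording length:** a chest monitor is fitted "with the objective of recording the heart rate beat by beat for 15 min, for later analysis of the HRV".
- **Filtering:** digital filtering is followed by "manual filtering (Microsoft Office Excel version 15.3) to eliminate premature ectopic beats and artifacts".
- **Inclusion of a recording:** "only sets with more than 95% of sinus beats will be included in the study".
- **Extract:** "From the period of greater stability of the tachogram, 1000 consecutive RR intervals will be extracted from the baseline and final moments".

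The section gives no rule for a recording that holds fewer than 1000 intervals.

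Two other sections bear on the point. The Outcomes section says that "the evaluative moments for all outcomes will correspond to the pre-intervention (M0", and the sentence goes on to M1 (after the last meeting) and M2 (four weeks later). The Statistical analysis section says: "All the randomized participants will be included in the analysis, in accordance with intention-to-treat principles". It fills missing values by last observation carried forward (LOCF) from M0 or M1.

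**The concern.** The article fixes the length of the recording in minutes and the length of the extract in beats. Whether the extract fits depends on each participant's heart rate, so the rule fails for an identifiable group, those with slow resting hearts. That group is not a random subset for this outcome, because resting heart rate is closely tied to the autonomic function that the HRV indices are meant to describe.

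Two things could happen to a short recording, and both cause trouble.

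- **It is dropped.** HRV is then missing in relation to the quantity being measured. LOCF cannot repair a missing M0, because there is no earlier value. A participant who falls below the limit only after baseline would have the M0 value carried forward, and the change would be recorded as zero.
- **It is analysed as it stands.** Segment lengths then differ between participants and possibly between visits. SDNN, among other indices, depends on segment length, so part of any difference would come from the processing.

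A smaller matter is that the extract is defined for a baseline and a final moment, while the Outcomes section names three assessments for all outcomes. It is not clear whether final means M1, M2 or both.

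**Working it through.** **Inputs from the protocol article (Secondary outcomes):** recording length 15 min; extract 1000 consecutive RR intervals; a recording must have more than 95% sinus beats, so just under 5% of beats may be non-sinus.

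**Input not in the article:** the distribution of resting heart rate. It is assumed below, for illustration only.

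**Step 1. Minimum heart rate.** Intervals available = mean heart rate × 15. Setting this to 1000 gives 1000/15 = 66.7 beats/min, which is a mean RR interval of at most 15 × 60,000/1000 = 900 ms.

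**Step 2. With filtering.** If 5% of beats are removed, the requirement becomes 1000/(15 × 0.95) = 70.2 beats/min.

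**Step 3. What a recording supplies at given rates.**

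| Mean rate (beats/min) | Intervals in 15 min | Minutes needed for 1000 |
|---|---|---|
| 50 | 750 | 20.0 |
| 55 | 825 | 18.2 |
| 60 | 900 | 16.7 |
| 65 | 975 | 15.4 |
| 67 | 1005 | 14.9 |
| 70 | 1050 | 14.3 |
| 75 | 1125 | 13.3 |
| 80 | 1200 | 12.5 |

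At 70 beats/min the extract takes 14.3 of the 15 minutes, which leaves 0.7 minutes of freedom to find the most stable stretch.

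**Step 4. Share affected, under assumption.** With a normal distribution of mean supine heart rate, the share below 66.7 beats/min is:

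| Assumed mean | SD 8 | SD 10 | SD 12 |
|---|---|---|---|
| 65 | 58% | 57% | 56% |
| 70 | 34% | 37% | 39% |
| 75 | 15% | 20% | 24% |

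Of the 60 participants planned in the Sample size section, 15% is 9 people (0.15 × 60) and 58% is about 35 (0.58 × 60). With the 70.2 beats/min limit of Step 2, the range rises to 27% to 74%.

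**Step 5. What LOCF would do if short recordings were dropped.** A missing M1 takes the M0 value, and a missing M2 takes the M1 or M0 value. A missing M0 cannot be filled. Someone below the limit at rest would usually be below it at M0 already, so LOCF gives no help to most of the affected group.

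**The case against.** The best counter-argument is that the article never says a short recording is excluded. The only stated inclusion rule is the one on sinus beats. A full protocol may say how short recordings are handled, and a condensed article need not repeat it. This stands as far as it goes: selective missingness is one of two possible consequences and is not stated in the text. It does not remove the conflict, because the article itself gives both figures and they cannot both be met below 66.7 beats/min.

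A reader might also infer that the rule biases the comparison between arms, for example because osteopathic treatment slows the heart and so treated participants lose more HRV data. The document does not support this. It gives no evidence that heart rate will change differently by arm. Being below the limit at M0 precedes allocation, since the envelope is opened after the initial assessment, so it is balanced between arms in expectation. A missing M1 or M2 would be filled by LOCF when an earlier value exists. A between-arm bias would need participants to cross the limit after baseline at different rates in the two arms. That is possible, but it remains conditional.

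It is also fair to say that no resting heart rate is given, so the share affected is unknown. The exclusion of cardiorespiratory disease does not fix a mean.

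Finally, the wording on baseline and final moments can be read as covering all post-baseline assessments, in line with the Outcomes section. It is loose wording and does not show that HRV is omitted at a visit.

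**Conclusion.** The point holds. The 15-minute recording and the 1000-interval extract are incompatible below a mean rate of 66.7 beats/min, or about 70 if 5% of beats are removed. This threshold is exact and rests on nothing outside the article. Just above it, choosing a stable period has little meaning.

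As written, HRV for slower-hearted participants would be either missing or computed on unequal segments, and the article does not say which. How many people this concerns is uncertain: the range of 15% to 58% depends entirely on the assumed normal distribution with mean 65 to 75 and SD 8 to 12 beats/min.

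The consequence is confined to HRV, one of the secondary outcomes. Pain, pressure pain threshold, disability and the sample size are not touched. The matter should be corrected before the HRV data are processed, but it does not threaten the trial's main conclusion.

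**What to change.** Replace the 1000-beat rule with a fixed-time segment that every 15-minute recording can supply, for example the most stable 5 minutes. Use the same length for every participant and every visit. Five of 15 minutes leaves real room to choose a stable stretch and to avoid ectopic beats. Replace the reference to baseline and final moments with M0, M1 and M2, as in the Outcomes section.

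This is a change in data processing. The Trial status section says that recruitment is under way, and recordings already made can be reprocessed in the same way without new visits. Lengthening the recording is less attractive at this stage, because it would mix recording lengths across participants and possibly within them.

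The cost is that shorter segments give somewhat noisier low-frequency indices. If the change is judged substantial, the Protocol amendments section also requires notice to the ethics committee and an update of the registry.

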### Participant timeline

The flowchart of the time schedule, interventions, assessments, and visits for participants is shown in Fig. 2.

### Sample size

The sample size was calculated to detect an effect between groups for the pain intensity outcome assessed using the numerical scale. For the calculation, a power of 80% and an alpha error of 5% were adopted and, based on the results obtained by Rizzo et al. [11], a standard deviation of 2.0 points and an average difference of 1.3 points were considered, which resulted in a total sample size of 52 individuals. Considering possible sample losses, there will be an increase of 15% in the sample size calculated, totalizing 60 participants. All calculations were performed on the software G*Power version 3.1.9.7 [34].

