Osteopathic manipulative treatment (OMT) is a hand-on part of osteopathic approach and a modality used in the treatment of LBP. Dal Farra et al., in a meta-analysis, presented strong evidence on pain reduction and improvement in function in LBP patients undergoing OMT [8]. The results presented by the systematic review by Louw et al. showed that, combining movement therapies, such as manual therapies, with education processes, it potentiated the effects on pain, function, disability, and psychosocial factors and also enabled improvement in movements and decreased use of health services in patients with chronic musculoskeletal pain [9].

Buttler and Moseley developed a method called pain neuroscience education (PNE). Addressing concepts of neurophysiology, neurobiology, representation, and meaning of pain, PNE aims to desensitize the neural system, contrary to the traditional anatomical and biomedical model [10]. In association with educational strategies, Rizzo et al. showed that clinical hypnosis (CH) enhances the results of education processes in patients with CLBP in the short and medium terms [11]. Thompson et al. in a meta-analysis totaling 3632 patients showed the effectiveness of CH as a pain re-education technique, producing moderate to great analgesia for all pain outcomes [12].

In view of the absence of standards in isolated allopathic or complementary treatments in the effectiveness of the treatment of CLBP, the growing number of researches in these areas of activity, and the absence of high-quality clinical trials that combine the aforementioned therapies in the management of this condition, our research is justified. This study aims to know whether OMT associated with PNE and CH is effective in the pain and disability of patients with CLBP in the short and medium terms or if the PNE and CH are sufficient in the management of these patients. We hypothesize that the combination of a physical approach such as OMT with PNE and CH can bring more benefits to this population, improving pain levels and reducing disabilities, in the short and medium terms.

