## Objectives

### Primary objective

The primary objective of the present study will be to evaluate the effects of PNE and CH associated with OMT on pain and disability in patients with CLBP compared to PNE and CH associated with sham therapy.

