### Interventions

Participants will be randomly divided into two groups (Fig. 1 and Fig. 2), called PNE + CH + OMT (intervention group) and PNE + CH + sham therapy (control group). For both groups, the participants will be submitted to PNE based on information from the book “Explain Pain” and CH [11, 15]. The intervention group will receive the same approach and additionally four OMT visits and the control group, sham therapy. For both groups, the meetings of OMT or sham therapy will be distributed in 30 min and 20 final minutes with a focus on education with PNE and CH. I All procedures (control and intervention group) will be carried out individually, once a week, with an interval of at least 7 days. Participants who cannot attend on the pre-scheduled days will be offered new dates within the study period, in order to avoid sample loss. All participants will be encouraged to report adverse events at any time to any researcher during the conduction of this study.

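### The 1.3-point difference used for sizing is justified only by a study of hypnosis added to education, so the 80% power has no stated empirical basis for OMT versus sham

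*Protocol article*

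**What the plan says.** The Sample size section sizes the trial on pain intensity between groups, on the numerical scale. It states that "a power of 80% and an alpha error of 5% were adopted". Citing the results of reference 11, it then gives its inputs and result: "a standard deviation of 2.0 points and an average difference of 1.3 points were considered, which resulted in a total sample size of 52 individuals". An extra 15% for losses brings the total to 60.

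The Background says what reference 11 found: "clinical hypnosis (CH) enhances the results of education processes in patients with CLBP in the short and medium terms".

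The Primary objective defines this trial's contrast as PNE and CH "associated with OMT on pain and disability in patients with CLBP compared to PNE and CH associated with sham therapy". The Interventions section confirms the shared background: "For both groups, the participants will be submitted to PNE based on information from the book", with hypnosis likewise given to both groups. The arms differ only in whether the 30-minute manual part of each visit is OMT or sham.

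**The concern.** As the Background describes it, reference 11 concerns what hypnosis adds to education. In this trial that component is the same in both arms, so its effect drops out of the comparison. The tested quantity is what OMT adds over a touch sham in participants who have all had education and hypnosis. The Sample size section does not say why a figure from reference 11 should apply to that quantity. It does not call 1.3 a smallest worthwhile difference, a target or an expected OMT effect.

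This matters because the protocol intends to interpret a null result. The end of the Background asks whether OMT helps or whether education and hypnosis suffice on their own, and the Discussion expects the trial to settle whether hands-on treatment is worth including. A non-significant result would be read against an 80% power figure that appears to rest on data, although those data concern another comparison.

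**Working it through.** **1. Contrast in the source and contrast in the trial**

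| | Differs between arms | Common to both arms |
|---|---|---|
| Reference 11, as described in Background | hypnosis | education |
| This trial (Primary objective, Interventions) | OMT versus sham | education and hypnosis |

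The component studied in reference 11 lies in the common column here.

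**2. Inputs (Sample size)**

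Difference 1.3, SD 2.0, so d = 1.3/2.0 = 0.65; alpha 5% (sidedness not stated); power 80%; total 52, or 60 after 52 × 1.15 = 59.8. Allocation is 1:1 (Study design and participants).

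**3. Reproducing the plan's 52**

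- Two-group comparison, two-sided, normal approximation: n per arm = 2 × (1.96 + 0.842)² × 2.0²/1.3² ≈ 37.2, so 38 per arm and 76 in total. The exact t-test gives 39 per arm, 78 in total.
- One-sided: 30 per arm, 60 in total.
- Repeated-measures ANOVA, between-groups effect, 3 measurements, correlation 0.5: f = 0.65/2 = 0.325; noncentrality = 0.325² × 52 × 3/(1 + 2 × 0.5) = 8.24; N = 52, power 80.4%.
- Baseline-adjusted ANCOVA with a baseline correlation of about 0.55 also gives 52.

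So 52 does not follow from the stated inputs by a two-group test. Among the variants tried, it appears only when a correlation that the text does not give is added. The three-measurement variant also treats the pre-treatment assessment (M0) as if it already carried the full difference, which overstates power.

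**4. Sensitivity to the difference, granting the plan's 80% at 1.3**

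The documents give no OMT-versus-sham figure on the pain scale, so the differences below are assumed. Power at 80% with two-sided 5% corresponds to a standardised difference of 1.96 + 0.84 = 2.80. For another true difference δ, power ≈ Φ(2.80 × δ/1.3 − 1.96).

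| δ | 2.80 × δ/1.3 − 1.96 | Power |
|---|---|---|
| 1.5 | 1.27 | 90% |
| 1.3 | 0.84 | 80% |
| 1.2 | 0.62 | 73% |
| 1.0 | 0.19 | 58% |
| 0.65 | −0.56 | 29% |

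The repeated-measures variant in step 3 agrees: 58% at 1.0 and 90% at 1.5 with N = 52.

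**5. Figures for a restated power paragraph (two-sided t-test, SD 2.0)**

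| | 52 analysed (26 per arm) | 60 analysed (30 per arm) |
|---|---|---|
| Power at 1.3 | 63% | 70% |
| Difference detectable with 80% power | 1.58 | 1.47 |
| 95% CI half-width | 2.009 × 2.0 × √(2/26) = 1.11 | 2.002 × 2.0 × √(2/30) = 1.03 |

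Step 5 follows from the stated inputs and the test used. It does not come from the mismatch in step 1.

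**The case against.** The best defence is that power is always conditional on an assumed difference. Having 80% power to detect 1.3 points is a coherent statement for any two-arm contrast, wherever 1.3 came from, and the protocol nowhere says that OMT is expected to yield 1.3. This stands. A reader might infer that the 80% is simply false for this trial; the documents support only that 1.3 has not been justified for OMT versus sham.

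Second, the text says that 1.3 was considered in light of reference 11's results. It does not say whether that was a between-group difference, a within-group change or a threshold used there. This also stands, and it rules out asserting that 1.3 is the hypnosis effect.

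Third, reference 11 is relevant to this trial: the protocol also cites it for eligibility, the education and hypnosis package and the pain scale. That supports it as a source for the SD, but not for the OMT increment.

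Fourth, a reader might infer that OMT's increment must be below 1.3 because both arms already receive active treatment. The documents do not show this. The Background cites strong evidence for OMT in low back pain (reference 8) and reports that combining manual therapy with education strengthens the effects (reference 9). It gives no comparator, scale or figure for reference 8, so that source could not be adopted unchecked either.

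Finally, the full protocol may hold a longer rationale. The article, however, names its source, and the named source concerns a different contrast.

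**Conclusion.** The point holds as a gap in justification. The only stated support for 1.3 is a study of a component that both arms here share, so the 80% power has no stated empirical basis for OMT versus sham. This rests on the Background's description of reference 11, since the source itself was not available.

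The consequence can be given only as the conditional range in step 4, and its direction is unknown. It would be wrong to attribute the 63% and 70% to the mismatch, or to conclude from it that the trial is underpowered. Those two figures assume a simple two-sided t-test with SD 2.0 and reflect that 52 does not follow from the stated inputs under that test. They belong in the remedy because a restated power has to be a figure that can be reproduced.

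The correction is worth making because it is cheap and because the protocol plans to draw a conclusion from a null result.

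**What to change.** Amend the Sample size section as follows:

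- Cite reference 11 as a source for the SD of 2.0 only.
- State 1.3 as the target (smallest worthwhile) difference for OMT versus sham on a PNE + CH background, with a justification for that contrast.
- Name the test, its sidedness and any correlation and number of measurements behind 52.
- Restate the power accordingly. If a simple two-sided t-test is used, the figures in step 5 apply: 63% or 70% at 1.3, and a difference of about 1.6 or 1.5 points detectable with 80% power, for 52 or 60 analysed.

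In the report, interpret a null result from the 95% confidence interval of the between-arm difference (expected half-width about 1.0 to 1.1 points) against the 1.3-point target. An interval that still includes 1.3 in favour of OMT would not show that education and hypnosis are sufficient.

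The cost is one paragraph and one line in the report, made through the route in the Protocol amendments section. No patients are added, and recruitment and procedures do not change. The downside is a less favourable stated power.

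### The stated inputs (difference 1.3, SD 2.0, 5% alpha, 80% power) need 78 participants for a two-group comparison, not 52; 52 gives about 63% power and 60 about 70%

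*Protocol article*

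**What the plan says.** The Sample size section of the protocol article says: "The sample size was calculated to detect an effect between groups for the pain intensity outcome assessed using the numerical scale". It gives the error rates ("a power of 80% and an alpha error of 5% were adopted"), and the effect with the result ("a standard deviation of 2.0 points and an average difference of 1.3 points were considered, which resulted in a total sample size of 52"). For losses, "there will be an increase of 15% in the sample size calculated, totalizing 60 participants". The software is G*Power. The section does not state the test, whether it is one- or two-sided, the number of measurements, any correlation between measurements, or any adjustment for baseline.

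The Study design section fixes 1:1 allocation. The Outcomes section sets three assessments: M0 before treatment, M1 after the last session and M2 four weeks later. The Statistical analysis section plans a two-factor repeated-measures ANOVA. It adds that "the analysis of the different moments between the groups will be carried out using" an unpaired t-test, or Mann-Whitney if the data are not normal. It plans no adjustment for baseline. All randomised participants are to be analysed, with the last observation carried forward.

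The aim at the end of the Background is to learn whether adding OMT is effective "or if the PNE and CH are sufficient in the management of these patients".

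**The concern.** The article gives a complete set of inputs for a two-group comparison of means together with a result, and the two do not match. This is a stated figure that is wrong for the comparison described, not a detail left to a fuller document.

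It matters because this is the trial's only power justification, and it concerns a primary outcome. If OMT really adds 1.3 points, a per-assessment t-test would miss it about 37% of the time with 52 analysed and about 30% with 60, not the 20% that readers are told. The Background also sets up a null result as a possible answer, namely that PNE and CH are enough without OMT. A reader who believes the power was 80% will give such a null result more weight than it can bear.

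**Working it through.** **Inputs.** From Sample size: difference 1.3, SD 2.0, alpha 5%, power 80%, N = 52 before losses and 60 after. From Study design: 1:1 allocation, so 26 or 30 per arm. Sidedness is not stated; two-sided is taken first.

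**Loss allowance.** 52 × 1.15 = 59.8, rounded to 60. This step agrees with the text.

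**Can 52 be reproduced as a two-group comparison?** The standardised difference is d = 1.3/2.0 = 0.65.

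- Normal approximation: n per arm = 2(1.960 + 0.842)²/0.65² = 37.2, so 38 per arm, 76 in total.
- Exact t-test (noncentral t, noncentrality d√(n/2), 2n − 2 degrees of freedom):

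| n per arm | Total | Two-sided 5% | One-sided 5% |
|---|---|---|---|
| 26 | 52 | 63.3% | 74.8% |
| 30 | 60 | 69.7% | 80.0% |
| 38 | 76 | 79.9% | – |
| 39 | 78 | 80.9% | – |

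The two-sided requirement is therefore 78. A one-sided test needs 60 before losses. Mann-Whitney at its usual relative efficiency of 0.955 needs about 39/0.955 = 40.8, so 41 per arm, 82 in total. None of these gives 52.

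**Detectable difference at 80% power (two-sided t-test).** 1.58 points with 26 per arm; 1.47 with 30 per arm.

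**Where 52 may come from.** This is a reconstruction, since the article names no procedure. G*Power's repeated-measures ANOVA, between factors, uses λ = f²·N·m/(1 + (m − 1)ρ) with f = d/2 = 0.325. With m = 3 measurements and ρ = 0.5, N = 52 gives λ = 0.1056 × 52 × 3/2 = 8.24 and power 80.4%; N = 50 gives 78.8%. So 52 is the answer for those settings. It is sensitive to ρ: 42 at ρ = 0.3 and 62 at ρ = 0.7. The route is not unique, because m = 2 with ρ = 0.3 also returns 52.

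**Does the three-measurement route support 80%?** That test compares group means averaged over M0, M1 and M2, and f = 0.325 assumes a 1.3-point difference at all three. Randomisation makes the expected difference at M0 zero.

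- Expected averaged difference: (0 + 1.3 + 1.3)/3 = 0.867.
- SD of a participant's average: 2√((1 + 2ρ)/3), which is 1.63 at ρ = 0.5.
- Power at N = 52: 47% (56% at ρ = 0.3, 40% at ρ = 0.7). At N = 60 and ρ = 0.5: 52%.

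**Group-by-time interaction.** Under the same pattern (0, 1.3, 1.3), this ANOVA term isolates a post-treatment difference:

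| ρ | N = 52 | N = 60 |
|---|---|---|
| 0.3 | 51% | 57% |
| 0.5 | 66% | 73% |
| 0.7 | 88% | 92% |

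**Baseline-adjusted comparison at one assessment.** The residual SD is 2√(1 − r²). At r = 0.5: 76% with 52 and 82% with 60. At r = 0.6: 82% and 87%.

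**Precision.** The 95% CI half-width is t × 2.0 × √(2/n): 2.009 × 2.0 × √(2/26) = 1.11 points with 26 per arm, and 1.03 with 30. Since 1.3 − 1.11 = 0.19, any observed benefit above about 0.2 points leaves 1.3 inside the interval when 52 are analysed. With 60 the limit is about 0.27.

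**The case against.** The strongest reply is that 52 is not an arithmetic slip. The first-named analysis is a repeated-measures ANOVA, there are three assessments, and the between-factors calculation with ρ = 0.5 gives 52. On that reading the unpaired t-test is only a follow-up, and the fault is an unreported or unsuitable procedure. This stands as a likely explanation of the number. It does not rescue the power claim, because the calculation needs a treatment effect before treatment.

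A second point is that the interaction is the more relevant ANOVA term and its power rises with the correlation, reaching 88% at 52 when ρ = 0.7. That is true, and it means 80% is attainable in this design under some assumptions. Others are baseline adjustment with r about 0.6 at 52, or the mean of M1 and M2 with ρ = 0.3 at 52 (81%). The article states none of these assumptions, and at ρ = 0.5 the interaction falls short at both sizes.

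Third, the planned analysis set is all 60 randomised, so 70% is the nominal t-test figure, and a one-sided 5% test with 60 gives 80%. But no one-sided test is stated, the extra eight are there only to cover losses, and carrying M0 or M1 forward does not restore the lost information. The protocol's own claim is that 52 is enough.

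Finally, the primary objective is an ordinary comparison, and nothing in the Statistical analysis section equates non-significance with sufficiency. That is fair: the risk of misreading is secondary, and the finding does not depend on it.

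**Conclusion.** The concern holds. For the between-group comparison described, with the stated SD, difference and alpha and a two-sided test, 52 participants give 63% power and 60 give 70%; 80% needs 78. The shortfall is 26 analysed participants or, equivalently, a detectable difference of 1.58 rather than 1.3 points at 52. The result assumes equal arms, the stated SD at the assessment compared, and no baseline adjustment, as the Statistical analysis section now stands. The origin of 52 in a repeated-measures calculation is an inference. Some analyses of the same data could reach 80%, but each needs a correlation that the article does not give.

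**What to change.** Keep the target of 60 and correct the Sample size section.

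1. Withdraw the statement that 52 gives 80% power for 1.3 points with SD 2.0. State the test, its sidedness, the number of measurements and any correlation that the calculation uses.
2. Then choose one basis:
   - **Unadjusted comparison at one post-treatment assessment.** Report about 63% power with 52 analysed (detectable difference 1.58) and about 70% with 60 (1.47).
   - **Baseline-adjusted comparison.** State the assumed baseline correlation. At r = 0.5 the power is 76% with 52 and 82% with 60. The Statistical analysis section must then name this comparison, because it plans none now.
3. Add a sentence that a non-significant result will not be reported as showing PNE and CH to be sufficient unless the 95% CI for the pain difference excludes the planned 1.3 points.

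No extra participants are needed. The cost is wording: on the first option a less favourable power figure, and on the second an explicit correlation assumption and a matching line in the analysis plan.
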